### Statistical methods

The statistical analysis will be carried out following the principles specified in the International Conference on Harmonization Topic E9 (CPMP/ICH/363/96). The data will be analyzed using the SPSS statistical software (version 22.0; IBM Corp).

A detailed statistical analysis plan will be available before the database is declared closed. A summary of the general approach to statistical analysis is presented. No intermediate analyses are foreseen.

A descriptive analysis will be performed for all parameters overall and by arm at every study time-point. Categorical parameters will be presented by means of frequencies and percentages. Continuous parameters will be summarized by means of the appropriate descriptive statistics (mean ± standard deviation or median and interquartile range).

The efficacy and safety endpoints will be descriptively compared between study arms. Changes from baseline, when applicable, will also be summarized by study arm.

#### Primary endpoint

The primary endpoint is the of patients who develop perianal fistula after surgery and during follow-up (6 months). An estimate of the effect size will be obtained using the relative risk (RR) with its corresponding 95% confidence interval (95% CI). If an imbalance is observed between the baseline characteristics of the two groups, the outcome will be adjusted for these characteristics by binary logistic regression analysis. The dependent variable will be the occurrence of perianal fistula within 6 months; the main independent variable will be the group to which the patient has been randomized and, as covariates, those variables that are unbalanced. In this case, the odds ratio (OR) will be estimated together with its corresponding 95% CI. The significance level is set at 0.05.

An interim analysis is not planned as there is no anticipation of significant safety issues, and, given the multicenter nature of the study, rapid recruitment completion is expected. Nevertheless, if safety issues are detected, the sponsor reserves the right to prematurely interrupt the study.

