### Sample size

To achieve 80% power to detect differences in the contrast of the null hypothesis *H*_0_:p1 = p2 using a bilateral chi-square test for two independent samples, taking into account that the significance level is 5%, and assuming that the proportion in the non-antibiotic group is 30%, the proportion in the antibiotic group is 15%, and that the proportion of experimental units in the reference group with respect to the total is 50%; it will be necessary to include 121 patients in the placebo group and 121 patients in the antibiotic group (242 patients in the study). Taking into account that the expected dropout rate is 15%, 143 patients per group would need to be enrolled, 286 patients in total.

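### Chance baseline imbalance decides whether the primary endpoint is adjusted, for which covariates, and whether an RR or an OR is reported, with no statement of which result decides

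*Protocol article*

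**What the plan says.** The Primary endpoint part of Statistical methods (protocol article) takes these steps in order.

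- It gives an effect measure without any condition: "An estimate of the effect size will be obtained using the relative risk (RR) with its corresponding 95% confidence interval (95% CI".
- It sets a trigger: "If an imbalance is observed between the baseline characteristics of the two groups, the outcome will be adjusted for these characteristics".
- The adjustment is a binary logistic regression on fistula by 6 months, with randomised group as main term and "as covariates, those variables that are unbalanced".
- The effect measure then changes: "In this case, the odds ratio (OR) will be estimated together with its corresponding 95% CI".
- One line on error control follows: "The significance level is set at 0.05".

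The adjusted model is not called secondary, supportive or a sensitivity analysis, and the RR is not said to stay primary when the model is fitted.

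Two other places bear on this. Sample size plans the trial "using a bilateral chi-square test for two independent samples", which is an unadjusted comparison. Statistical methods presents its text as a summary and promises that "A detailed statistical analysis plan will be available before the database is declared closed".

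**The concern.** Allocation is randomised 1:1, so a baseline difference between arms is a chance event if randomisation was done properly. A covariate is worth adjusting for when it predicts fistula. The rule ignores that: it can bring in a variable unrelated to fistula because it happened to differ, and leave out a strong predictor because it happened to match.

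The rule also makes the form of the primary result depend on the data. The covariates, and whether the reader is given an RR or an adjusted OR, are known only once baseline data have been split by arm. With one significance level and no stated order between the two results, a trial in which they fall on opposite sides of 0.05 has no agreed answer. The Discussion presents this trial as a response to contradictory evidence, so a result that turns on the choice of model would be unhelpful.

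**Working it through.** **1. The plan's own figure.** Inputs from Sample size: 30% against 15%, two-sided 5%, 80% power, equal arms. With pooled variance under the null and no continuity correction:

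n = [1.96·√(2·0.225·0.775) + 0.8416·√(0.30·0.70 + 0.15·0.85)]² / 0.15² = (1.1575 + 0.4889)² / 0.0225 = 120.5, so 121 per arm.

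Dropout: 121/0.85 = 142.4, so 143 per arm. Both stated figures reproduce; power at 121 per arm is 80.2%. The trial is sized on the unadjusted comparison.

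**2. The two effect measures differ.** At the design rates RR = 0.15/0.30 = 0.50, and the unadjusted OR = (0.15/0.85)/(0.30/0.70) = 0.41. An OR adjusted for prognostic covariates is a different quantity again.

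**3. How often the trigger fires.** The article gives neither the number of baseline variables nor a threshold, so both are assumed here. For K independent variables each tested at 5%, P(at least one flagged) = 1 − 0.95^K:

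| K | 5 | 8 | 10 | 15 | 20 |
|---|---|---|---|---|---|
| P | 23% | 34% | 40% | 54% | 64% |

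If imbalance instead means an absolute standardised difference above 0.1, the standard error with 121 per arm is √(2/121) = 0.129. Each variable is then flagged with probability P(|Z| > 0.1/0.129) ≈ 0.44, and for K = 10, 1 − 0.56^10 is above 99%. The threshold largely settles which analysis is run.

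**4. Power at the design rates.** Simulation with 121 per arm, 30% against 15%, 8 assumed covariates of which 2 are prognostic, imbalance judged at 5%, 3000 trials (Monte Carlo error about 0.7 points). About a third of trials were flagged.

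| Prognostic strength per SD | Unadjusted | Plan's rule | Always adjusted for the 2 prognostic covariates |
|---|---|---|---|
| log-OR 0.4 (OR about 1.5) | 80.7% | 80.5% | 82.0% |
| log-OR 0.7 (OR about 2.0) | 81.3% | 81.1% | 86.0% |

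The rule performs like the unadjusted test. Fixed adjustment gains 1.5 points in the first row and 4.9 in the second.

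**5. Type I error and disagreement.** A second simulation used 10 assumed covariates, 3 prognostic (log-OR 0.3 or 0.6 per SD), 121 per arm, 4000 trials per scenario.

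- Trigger rate: 40-42% under p < 0.05, and 99.6% or more under the 0.1 rule.
- No treatment effect: the rule rejects in 3.8-5.2% of trials. Claiming success if either analysis is significant rejects in 5.1-6.2%.
- True effect: the unadjusted and rule-based results disagree on significance in 2.1-4.3% of trials under p < 0.05, and in 7.0-11.1% under the 0.1 rule.
- True effect, power, rule against fixed adjustment: 74-75% against 76-77% at log-OR 0.3, and 69-71% against 75-76% at log-OR 0.6.

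Absolute power is lower here because the treatment log-OR of −0.887 (the log of 0.41) was applied conditionally on the covariates, so the marginal rates are not exactly 30% and 15%. The contrast between strategies matches step 4.

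**The case against.** The strongest reply is that this is a condensed article with a SAP to come. A conditional rule can be pre-specified: the SAP may list candidate variables, set a threshold and state which result decides. That is right. The missing threshold and list are not faults in themselves, and a reader who infers that the analysis cannot be pre-specified goes too far. But the article does state a rule. A SAP that follows it would still have its fitted covariates selected by observed imbalance, and a SAP that fixed one model would depart from it.

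A reader might also infer that the adjusted OR replaces the RR as the deciding result. The text does not say so. The RR sentence carries no condition, and sizing on an unadjusted chi-square test supports reading the logistic model as supplementary. Against that, adjustment is worded as something that will happen to the outcome, with no order given. Both readings are open, and that openness is the point.

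A third inference is that the model must be chosen after unblinding. Checking balance needs only group labels, and coded arms would serve. The article does not say whether they will be used. Data collection and management has the data locked before analysis, which prevents changes to the data but not choices about the model.

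Finally, an unadjusted primary analysis is legitimate, and the power shortfall is measured against a different design, not against the 80% promised. That stands too.

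**Conclusion.** The point holds in a limited form. The protocol article lets chance imbalance between randomised arms determine covariate adjustment and the effect measure for its primary endpoint, and leaves open which result decides at 0.05.

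It does not hold as a claim of inflated error or an underpowered trial. Applied mechanically, the rule keeps type I error near 5% and, at the design rates, power near 80%. Even free choice between the two analyses takes the error only to about 5-6%. What is lost is a determinate primary result, protection against analyst discretion, and some precision: about 1-2 points of power with moderate prognostic covariates and about 5 with strong ones. Disagreement between the two results on significance ranges from about 2% to 11% of trials, depending mostly on how imbalance is defined.

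These sizes rest on assumed numbers, independence and strength of covariates and on assumed thresholds, since the article gives none. The objection to the criterion itself rests only on the randomised design and the wording of the rule.

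**What to change.** Delete the imbalance trigger and name one primary analysis before anyone compares the arms. Either choice below cures the defect.

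- **Unadjusted:** the RR with 95% CI and the two-sided chi-square test on which the trial was sized. The 121 analysed and 143 enrolled per arm stand as they are.
- **Adjusted in every case:** a model with centre and a short list of covariates fixed in advance on expected prognostic value, whatever the baseline table shows. State its effect measure, for example a standardised RR or risk difference with 95% CI, so that the RR/OR ambiguity does not return. The article names no predictors of fistula (age and BMI appear only as eligibility limits), so the investigators would have to justify the list.

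Report the other analysis, and any adjustment prompted by observed imbalance, only as sensitivity analyses that cannot replace the primary result. Show the baseline table by arm for description, not for choosing the model.

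The cost is wording in the protocol and SAP, with no added patients. The small downside is that the covariates and the order of analyses must be settled before by-arm data are seen.

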### Plans to give access to the full protocol, participant-level data, and statistical code

These plans are not yet in place.

### Trial monitoring

The Clinical Trial Unit of Instituto de Investigación Sanitaria Puerta de Hierro-Segovia de Arana is responsible for project management, regulatory compliance, and trial monitoring.

The day-to-day support of the trial will be carried out by the principal investigator of the study, with the support of the members of the Clinical Trial Unit at the coordinating center, maintaining continuous contact with the principal investigators at each participating center.

### Adverse event reporting

Serious adverse events (SAEs) and grade 3 or 4 adverse events will be collected from the time of informed consent to day 29. SAEs will be followed up until the SAE has subsided, returned to baseline, or is stable.

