**Discussion:**

This clinical trial is designed to evaluate the efficacy and safety of amoxicillin/clavulanic in the prevention of perianal fistula. The results of this study are expected to contribute to stablish the potential role of antibiotherapy in the therapeutics for anal abscess.

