#### Safety and tolerability assessment

According to EMA recommendations (EMA/CPMP/EWP/280/96 Corr1), systemic safety shall be assessed on the basis of the adverse event record, the physical examination of patients, and the results of analytical studies.

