## Discussion

Much controversy exists regarding the prophylactic use of antibiotics in the development of AF after incision and drainage of an AA. Its use is controversial and only weakly supported by current guidelines due to low-quality evidence [12]. To the best of our knowledge, there are only 2 clinical trials that have evaluated the use of prophylactic antibiotic therapy in this setting with in some cases inconclusive and contradictory results. Sözener et al. [6] concluded that antibiotic therapy with amoxicillin plus clavulanic acid had no protective effect regarding risk of fistula formation vs placebo at 1 year follow-up after surgical drainage of anorectal abscesses. This study could have had a negative result due to a low statistical power. On the other hand, Ghahramani et al. [5] concluded that postoperative prophylactic antibiotic therapy including ciprofloxacin and metronidazole play an important role in preventing fistula in-ano formation vs placebo at 3 months follow-up. In this study, a single dose of ceftriaxone was administered peri-surgically in both groups and 2 antibiotics other than the one we will assay in our study were used. As an additional difference, in this study only a 3-month follow-up was performed. A recent meta-analysis [16] on this issue concluded that further randomized trials are needed to fully clarify the role, duration, and type of antibiotics best suited for postoperative prevention of fistula following drainage of anorectal abscesses because the quality of evidence is low.

Thus, there is a substantial need to conduct appropriately powered randomized controlled studies in order to generate a reliable and conclusive evidence regarding the benefits and risks of these therapies. Our hypothesis is that the combination of amoxicillin and clavulanic acid will reduce the incidence of anal fistula.

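### The adverse event collection rule (SAEs and grade 3 or 4 events to day 29) does not support the tolerability part of the safety and tolerability outcome

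*Protocol article*

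**What the plan says.** Under Secondary outcome measures, the protocol article has a subsection headed "Safety and tolerability assessment". It states that "systemic safety shall be assessed on the basis of the adverse event record, the physical examination of patients, and the results of analytical studies". It sets no grade limit on the adverse event record.

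The abstract's Discussion paragraph says: "This clinical trial is designed to evaluate the efficacy and safety of amoxicillin/clavulanic in the prevention of perianal fistula". Statistical methods plans a descriptive comparison of safety endpoints between the arms.

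Only the section Adverse event reporting gives the scope of collection, in these words: "Serious adverse events (SAEs) and grade 3 or 4 adverse events will be collected from the time of informed consent to day 29". The next sentence adds that "SAEs will be followed up until the SAE has subsided, returned to baseline, or is stable".

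Treatment is a one-week oral course of active drug or placebo (Intervention description). Follow-up for the primary outcome is 6 months.

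**The concern.** One section names an outcome, and another defines the data for it too narrowly. Tolerability is mostly a matter of mild and moderate symptoms and of whether patients give up the tablets because of them. The eligibility criteria exclude diabetes, immunosuppression, signs of severe sepsis and morbid obesity, so severe events during a one-week course can be expected to be few. A record limited to SAEs and grade 3 or 4 events would then be nearly empty in both arms.

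A sparse table could be read as good tolerability when it mainly reflects the collection rule. If the drug does prevent fistulas, the case for giving it to every drained patient has to be weighed against the intolerance it causes. The trial as described would have little to say on that, and events not recorded during treatment are hard to recover later.

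**Working it through.** **Step 1: set the sections side by side.**

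| Element | Safety and tolerability assessment | Adverse event reporting |
|---|---|---|
| Subject | safety and tolerability | collection of adverse events |
| Severity | no limit stated | SAEs and grade 3 or 4 |
| Window | not stated | consent to day 29 |
| Other sources | physical examination, laboratory results | none |

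Non-serious grade 1 or 2 events fall within the subject of the left column and outside the rule in the right column. No other section provides for them. Examination and blood tests do not reliably capture symptoms that a patient reports, or tablets stopped because of them.

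**Step 2: check the window.** The course lasts 7 days, so collection to day 29 runs about 29 − 7 = 22 days past the last treatment day. The window is adequate for the treatment period; the gap lies in the grades collected.

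**Step 3: reproduce the plan's own figure.** With 30% versus 15%, two-sided 5% and 80% power, the pooled-variance formula gives

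n = [1.96·√(2·0.225·0.775) + 0.8416·√(0.30·0.70 + 0.15·0.85)]² / 0.15² = 1.6464² / 0.0225 ≈ 120.5, so 121 per arm.

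With 15% dropout, 121 / 0.85 = 142.4, so 143 per arm. Both figures match the Sample size section. They serve the primary outcome and do not depend on this point.

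**Step 4: what 143 per arm could show.** The article gives no adverse event rates, so every rate below is an assumption.

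Severe events only:
- Expected number at 1%: 143 × 0.01 = 1.43.
- Chance of none in one arm: 0.99^143 = 0.24 at 1%; 0.995^143 = 0.49 at 0.5%; 0.98^143 = 0.06 at 2%.

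Power = Φ[(d − 1.96·SE0) / SE1], where d is the difference, SE0 = √(2·p̄(1 − p̄)/n) and SE1 = √([p1(1 − p1) + p2(1 − p2)]/n). For 5% versus 15%, SE0 = 0.0355 and SE1 = 0.0350, so (0.10 − 0.0695)/0.0350 = 0.87 and power is 81%.

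| Record | Assumed rates | Power at 143 per arm |
|---|---|---|
| Grade 3–4 | 1% vs 2% | 10% |
| Grade 3–4 | 1% vs 3% | 23% |
| All grades | 5% vs 10% | 36% |
| All grades | 10% vs 20% | 66% |
| All grades | 5% vs 15% | 81% |
| All grades | 5% vs 20% | 97% |

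The planned comparison is descriptive, so precision is the fairer measure. For 5% versus 15%, the 95% CI half-width for the risk difference is 1.96 × 0.0350 = 6.9 percentage points. For 10% versus 20% it is 1.96 × 0.0418 = 8.2 points.

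**Step 5: patients affected but not recorded.** If 5% and 15% had an event of any grade, that is 7.2 and 21.5 patients of 143. If 1% in each arm had a severe event and were therefore recorded, about 7.2 − 1.4 = 5.7 and 21.5 − 1.4 = 20.0 patients would have only events outside the collection rule.

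**The case against.** The article condenses a full protocol that is not shown, and the visit schedule in Fig. 1 is missing. The collection rule does not contain the word *only*, so wider recording elsewhere cannot be excluded. That stands as a limit on certainty. It does not remove the point, because the article is not silent: it states a scope by seriousness, grade and time, and naming grades 3 and 4 would serve no purpose if all grades were collected. If the full protocol does collect them, the article's sentence needs correcting.

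Some existing records touch on the matter: the reason for leaving the study goes on the case report form, concomitant medications are listed, and accountability records are monitored. These are partial substitutes. Leaving the study is not the same as stopping tablets, and none of them replaces an all-grade event form.

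A reader might go further and infer any of the following, which the article does not support:
- *The trial cannot assess safety at all.* Serious and severe events are collected, and the outcome also draws on examination and laboratory results.
- *Day 29 is too early because follow-up lasts 6 months.* The window covers the course and about three further weeks, and SAEs already reported are followed to resolution or stability. Nothing in the article calls for collecting new SAEs to month 6.
- *The trial promises conclusive evidence on risks.* The phrase "generate a reliable and conclusive evidence regarding the benefits and risks of these therapies" in the main Discussion describes a need for studies in the field. The claim made for this trial is the abstract's, and it speaks of safety, not tolerability.
- *Early stopping for safety is compromised.* The sponsor's right to interrupt the trial is not tied to any particular record, and serious and severe events are the ones most relevant to it.

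**Conclusion.** The mismatch is real and limited. As described, collection does not support the tolerability part of a named secondary outcome, because non-serious grade 1 or 2 events and tablet stops due to them are not provided for. A limited safety assessment remains possible.

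The numerical size cannot be fixed from the article. Under the assumed rates, grade 3 or 4 events alone would say little about a difference between arms (power 10% to 23%). All-grade recording in the same sample could be informative if the difference is 10 percentage points or more (66% to 97%), and much less so for 5% versus 10% (36%). The conclusion rests on reading the collection rule as complete, which is natural but inferred. The primary outcome, its analysis and the sample size are not affected. This is a cheap improvement and no threat to the trial's main result.

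**What to change.** Reconcile the two sections in one of two ways.

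**Preferred.** Amend Adverse event reporting to record adverse events of all grades from informed consent to day 29, keeping the present window. Record grade, relatedness and whether study tablets were stopped. Report by arm the percentage of patients with any event, with any event leading to stopping tablets, and with any grade 3 or higher event, each with a risk difference and 95% CI. The cost is a wider eCRF form, more data entry and a protocol amendment. Recruitment began in April 2022 and was expected to finish by the end of 2024, so all-grade data would exist only for patients enrolled after the change. The analysis must state that date and restrict all-grade comparisons to those patients.

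**Otherwise.** Narrow the secondary outcome, and the safety claim in the abstract, to serious and severe events together with examination and laboratory findings, and make no statement on tolerability. This costs only wording, but leaves tolerability unanswered.

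If the full protocol already collects all grades, correcting the sentence under Adverse event reporting is enough.

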### Plans for auditing trial conduct

Monitoring online visits will include, but not limited to, review of regulatory files, accountability records, CRFs, ICFs, medical and laboratory reports, site study intervention storage records, training records, and protocol and GCP compliance. On-site and off-site monitoring, central review of data collection, and remote source data verification will be allowed.

